### **(iii) Study design**

**(a) Clinical assessment:** The primary outcome will be evaluated using BDI-II, one of the most widely used psychometric tests for measuring the severity of stress trauma-related depression.[21] The secondary outcomes are clinician-assessed depression, stress, PTSD symptoms, insomnia and quality of life that will be assessed with HAMD-17, PSS, PCL-C, ISI and SF-12, respectively. These instruments have been widely used in domestic violence studies. Adverse events will be assessed using the standardized case report forms. The aforesaid instruments have been extensively implemented in our previous studies. Assessment will be performed at baseline, Week 3, Week 6, and Week 12. The reason for Week 3 as the earliest measurement point is based on our previous TEAS and DCEAS studies, showing that the significant improvement was observed at as early as at Week 3.

**(b) Maintenance of fidelity and consistency:** As participants will conduct TEAS themselves at home, they are required to record their TEAS sessions in a log sheet on the daily basis. Meanwhile, we will send a reminder to participants by mobile phone, monitor their TEAS treatment, answer their questions, and receive their emergency report.

The study will last about 3 years and be carried out in multiple sites. There also will be many different professional investigators involved in the study. To ensure consistency of DCEAS and assessment across sites and throughout a study period, training workshop will be conducted at pre-trial and once per year thereafter. All investigators and caregivers will receive training. Training manual will be prepared. For DCEAS, the PI and a senior acupuncturist will instruct and demonstrate DCEAS. Trainees are required to obtain satisfactory training outcomes which will be rated by the PI and a senior acupuncturist. For clinical assessment training, an investigator who has extensive experience in clinical assessment will instruct clinical instruments. A depressed patient video will be used for the measurement of BDI-II. An inter-rater reliability coefficient (k value) of >0.80 must be achieved after the completion of each training workshop.

To further ensure consistency and fidelity, the following additional measures will be taken: (1) All assessments from baseline throughout endpoint for each participant will be performed, if possible, by the same assessor who is blind to participants' intervention; (2) all DCEAS sessions of each patient will be conducted by the same acupuncturist, if possible; and (3) biomarker analysis will be done by the same research assistant.

**(c) Safety assessment, assurance and ethical consideration:**

For each visit to treatment, a standardized case report form will be used to record patients' AEs, including whether any AE has occurred, occurrence time, duration, type of event, severity, management, and its outcome. Also, whether the adverse events are caused by acupuncture would be assessed. The Common Terminology Criteria for Adverse Events (CTCAE) v5.0 criteria will be used to evaluate the severity of each adverse event [22]. All associated research staffs are trained to recognize and respond to all the adverse events. If an adverse event is regarded as a serious adverse event, it will be reported to project investigators ([name]) and Ethics Committee to review immediately. They will decide whether the patient will be temporarily/permanently interrupted from their current treatment, whether

the patient will withdraw from this clinical trial and whether this trial needs to be adjusted or terminated.

Case Record Form (CRF) will be used to record patients' information, assessment, and treatment. In addition to mobile phone, emergency contact numbers will be provided to participants for them to report emergency and seek advice. Ethical approval will be obtained before the recruitment starts. All participants are required to provide written consent. The proposed study will be registered in [www.clinicaltrials.gov](http://www.clinicaltrials.gov).

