#### **(iv) Data processing and analysis**

##### **(a) Data management**

Data will be collected by blinded independent assessors and entered into a password-protected computer using a double entry method. Each participant will be assigned an identification number for data processing and communication. Personal data will be stored and protected in accordance with the requirements of the Hong Kong Personal Data (Privacy) Ordinance (CAP 486). The deidentified data will be used for analysis and publication. The publication of any results will not reveal the identity of any participant. The results will be provided to the participants and social workers in a short summary after the publication of the trial if required. To prevent patient attrition, research assistants will confirm appointment information with participants and send a reminder before the scheduled appointment. In addition, a transport allowance will be provided to each participant upon completion.

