| INTERVENTIONS (TEAS+DCEAS): |              |            |                 |    |    |
| Treatment group             |              |            | ←————→          |    |    |
| Routine care group          |              |            |                 |    |    |
| ASSESSMENT:                 |              |            |                 |    |    |
| BDI-II                      | X            | X          | X               | X  | X  |
| AAS                         | X            | X          | X               | X  | X  |
| HAMD-17                     |              | X          | X               | X  | X  |
| PCL-C                       |              | X          | X               | X  | X  |
| PSS-10                      |              | X          | X               | X  | X  |
| ISI                         |              | X          | X               | X  | X  |
| SF-12                       |              | X          | X               | X  | X  |
| Adverse Events              |              | X          | X               | X  | X  |
| Blood Sampling              |              | X          |                 |    | X  |

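### The protocol places adverse-event collection in two ways: one puts the HAMD-17 rater's blinding at risk, the other ascertains events unequally between the arms

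*Protocol*

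**What the plan says.** The relevant text is spread over five places in the protocol.

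- **C(iii)(a) Clinical assessment** lists adverse events after the outcome scales: "Adverse events will be assessed using the standardized case report forms". It then sets the times for the whole list: "Assessment will be performed at baseline, Week 3, Week 6, and Week 12".
- **Fig. 4** has an "Adverse Events" row in its assessment block, marked at T0 to T3 (Weeks 0, 3, 6 and 12), the same columns as HAMD-17.
- **C(iii)(b) Maintenance of fidelity and consistency**: "All assessments from baseline throughout endpoint for each participant will be performed, if possible, by the same assessor who is blind to participants' intervention".
- **C(iv)(a) Data management**: "Data will be collected by blinded independent assessors and entered into a password-protected computer using a double entry method".
- **C(iii)(c) Safety assessment** gives a different occasion: "For each visit to treatment, a standardized case report form will be used to record patients' AEs". The form covers, among other things, the type of event and its management. The section then adds: "Also, whether the adverse events are caused by acupuncture would be assessed". It does not say who completes the form or who judges cause.

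Three other statements bear on the point. The control arm may have TEAS or DCEAS only after completing the trial (C(ii)(e)). DCEAS is given twice a week for 12 weeks (C(ii)(c)). The data analysis section compares the incidence of adverse events by chi-square or Fisher's exact test.

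**The concern.** The trial is described as assessor-blinded, it has no sham, and participants know their arm. HAMD-17 is the outcome the protocol expressly calls clinician-assessed, so its protection against expectation bias rests on the rater not knowing the arm. A structured adverse-event interview invites the kind of answer that reveals it: a complaint at a needle site or under an electrode pad can come only from the acupuncture arm. A rater who is blind also has no sound basis for saying whether acupuncture caused an event.

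Moving the form to treatment visits, as the safety section suggests, creates a different problem. Only the acupuncture arm has treatment visits run by the trial. More frequent questioning finds more events, so an incidence comparison would mix a real difference in harm with a difference in how often women were asked.

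**Working it through.** The protocol gives no figure on this point to reproduce. The check is to follow each reading to its consequence and count contacts.

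**Reading A: adverse events belong to the scheduled assessments.**
1. C(iii)(a) and Fig. 4 place adverse events with the assessments at Weeks 0, 3, 6 and 12.
2. C(iii)(b) gives all assessments, where possible, to one blinded assessor per participant. C(iv)(a) gives data collection to blinded assessors. Neither excepts adverse events.
3. So the person rating HAMD-17 also asks about adverse events. The baseline contact is harmless, because the allocation envelope is opened only after the baseline assessments. The three later contacts are not.
4. Number of such contacts in the acupuncture arm: 55 women × 3 visits = 165 at most. With the planned 20% dropout, completers number 55 × 0.8 = 44, and they alone give 44 × 3 = 132. These are opportunities for disclosure, not unmasked ratings.
5. Because the same assessor is kept, a disclosure persists. If the form precedes HAMD-17 at Week 3, a disclosure there touches the ratings at Weeks 3, 6 and 12. If it follows, it still touches Weeks 6 and 12. The order of the two within a visit therefore does not solve the problem while one person does both.

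**Reading B: the form belongs to treatment visits.**
1. The safety section ties the form to each visit to treatment. DCEAS visits number 2 per week × 12 weeks = 24 per woman in the acupuncture arm. TEAS is self-administered at home and adds no clinic visit.
2. The control arm has no trial treatment visits. Its routine care continues as before and is not delivered by the trial.
3. Scheduled contacts at which events are sought, acupuncture against control:
   - treatment visits only: 24 against 0;
   - treatment visits plus the Fig. 4 assessments: 24 + 3 = 27 against 3.
4. The between-arm test of incidence then compares arms with unequal ascertainment. In the second case the control events also come from the visits given to blinded assessors, so Reading A's problem remains.

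Neither reading gives collection that is both equal between arms and separate from outcome rating.

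**The case against.** The strongest reply is that the safety section itself points away from the blinded assessor. It attaches the form to treatment visits, where a practitioner who knows the allocation is present, and it sends serious events to the project investigators. The other passages are weaker evidence: Fig. 4 gives timing, not personnel; the same-assessor rule is about consistency and holds only if possible; and the data-management sentence is general. Taken literally, it would have blinded staff collect the treatment records as well. A form with the same questions in both arms does not reveal the arm unless the answer does. Without a sham, women could disclose their arm in any interview.

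Most of this stands. A reader might infer that the plan has the blinded assessor judge causality, or that safety collection necessarily unblinds the HAMD-17 rater. The documents support neither. No passage names the causality rater, and what they show is a risk, on top of the background risk of spontaneous disclosure.

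The reply does not clear the plan, however. If treating staff complete the form at treatment visits, ascertainment is lopsided and the incidence comparison is no longer like for like. Nor is this a detail that can wait for the analysis plan: who collects adverse events, and when, is trial conduct, and here the protocol's sections disagree.

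**Conclusion.** The point holds as an unreconciled assignment with a cost on either side. On the assessment-visit reading, HAMD-17 blinding is put at risk, one-sidedly in the acupuncture arm. On the treatment-visit reading, adverse events are sought at up to 24 DCEAS visits in one arm and at none, or at 3 assessments, in the other, which biases the incidence comparison.

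No bias size can be derived. The documents give neither the share of women who would mention a procedure-specific event nor the shift in a rating once the arm is known, and any figure would be assumption alone. The contact counts assume full attendance.

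The exposed endpoint is mainly the secondary HAMD-17. The primary BDI-II, and response and remission, which are defined on it, are not shown to be affected. The rater training and agreement threshold for BDI-II in C(iii)(b) hint at an assessor role there too, but the protocol does not say what that role is. The change is worth making because it is cheap and helps on either reading.

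**What to change.** Reconcile C(iii)(a) to (c), C(iv)(a) and Fig. 4 so that they state the following:

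- For the between-arm comparison, adverse events are collected at Weeks 3, 6 and 12, with the same questions in both arms, by a named existing team role that does not rate outcomes, after the HAMD-17 is complete. The same-assessor and blinded-collection sentences should except adverse events.
- Reports arising at treatment visits are recorded separately by treating staff and are not pooled into the between-arm incidence test.
- Causality is judged by unblinded investigators.
- Participants are asked not to mention their treatment to the outcome assessor.

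The route for serious events stays as it is. The cost is protocol wording and reassigning an existing form. A research assistant could take it on, but the protocol does not say that research assistants never rate outcomes, so the role must be fixed explicitly. The small downside is that two interviews must be scheduled in sequence at each visit.

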#### **(iv) Data processing and analysis**

##### **(a) Data management**

Data will be collected by blinded independent assessors and entered into a password-protected computer using a double entry method. Each participant will be assigned an identification number for data processing and communication. Personal data will be stored and protected in accordance with the requirements of the Hong Kong Personal Data (Privacy) Ordinance (CAP 486). The deidentified data will be used for analysis and publication. The publication of any results will not reveal the identity of any participant. The results will be provided to the participants and social workers in a short summary after the publication of the trial if required. To prevent patient attrition, research assistants will confirm appointment information with participants and send a reminder before the scheduled appointment. In addition, a transport allowance will be provided to each participant upon completion.

##### **(a) Data analysis**

One biostatistician who is blinded to interventions will be responsible for statistical analysis. Descriptive statistics tables will be used to present basic information on all variables. For continuous variables, the mean and standard deviation (or medians, 25th, and 75th percentiles) will be presented; while for categorical variables, the number of participants in each category and its percentage will be presented separately. The analysis will be carried out on the intention-to-treat (ITT) population. All eligible participants will be included in the analysis. Missing data on the primary outcome will be imputed using the multiple imputation method under the missing at random (MAR) assumption followed by sensitivity analysis.

The primary outcome will be analyzed by a linear mixed-effects model with repeated-measures, with adjustment for the baseline; visit, treatment, and the visit  $\times$  treatment interaction as the fixed effect, and individual subject as the random effect. A significant two-way interaction will be considered to demonstrate whether the treatment group has a greater change in the BDI-II score from baseline to assessing points than the routine care group. The effect of the treatment will be estimated by the difference between treatments, and will be presented together with its associated 95% confidence intervals (CIs). A similar approach will be applied to other continuous outcomes.

For the response rate and remission rate, logistic regression, with adjustment for baseline scores, and Chi-square ( $\chi^2$ ) test will be used. The definition of responder is subjects with  $\geq 50\%$  reduction from the baseline BDI-II score; the definition of remission is subjects with BDI-II score less than 10. Subjects who discontinue treatment prior to having a post-baseline BDI-II score will be considered non-responders/not remission.

Subgroup analysis will be further conducted to detect whether demographic and baseline clinical variables are associated with outcomes. Student t-test and Wilcoxon rank sum test will be used to detect differences in continuous baseline variables and biomarker levels between the two groups. Categorical baseline variables, including discontinuation and incidence of adverse events will be analyzed using Chi-square ( $\chi^2$ ) test or Fisher's exact tests. Linear mixed-effects model will be conducted to examine intercorrelations between clinical outcomes and biomarker levels and among biomarker levels. Statistical significance is defined as a two-tailed  $P < 0.05$ .

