**(c) Estimation of sample size:**

The sample size for this trial was estimated based on our preliminary trials [9, 15]. According to previous established HAMD-17 to BDI-II conversion metrics [20], the results indicating an approximately difference of 6.55 in the BDI-II score between two groups. A sample size of 55 in each group will be sufficient with a 95% level of significance ( $\alpha$ ), 80% power ( $1 - \beta$ ), and a conservatively assumed standard deviation of 10.8, and a dropout rate of 20%. Therefore, this trial will include 110 subjects.

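### With a subject random effect as the only stated covariance term, visit-specific BDI-II intervals such as Week 12 have the wrong width if the variance differs between visits

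*Protocol*

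**What the plan says.** The Data analysis section of the protocol gives the primary model: "The primary outcome will be analyzed by a linear mixed-effects model with repeated-measures, with adjustment for the baseline". Visit, treatment and their product follow, with the "interaction as the fixed effect, and individual subject as the random effect". No residual covariance structure, random slope, visit-specific variance or robust standard error is mentioned. The claim of benefit is tied to a significant visit × treatment interaction. The treatment effect is reported as a between-arm difference with a 95% interval, and no visit is named for it. The other continuous outcomes are to be handled in a similar way.

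The Clinical assessment paragraph sets the visits: "Assessment will be performed at baseline, Week 3, Week 6, and Week 12". With baseline as a covariate, three repeated measurements are modelled. The sample-size section gives a single spread, "a conservatively assumed standard deviation of 10.8", without tying it to a visit, and no correlation between visits.

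**The concern.** A subject intercept with independent residuals is compound symmetry: the same variance at every visit and the same correlation for every pair of visits. When a difference at one visit is taken from such a model, its standard error uses a variance pooled over all three visits rather than the variance at that visit.

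Week 12 is the end of treatment and a natural difference to report. If BDI-II scores, after baseline adjustment, are more spread out at Week 12 than at Week 3, the model understates the Week 12 standard error, and the interval is too short. Such growth is plausible. Entry requires a BDI-II of at least 14, routine care differs between women, and a baseline score usually predicts less well as time passes. It is not shown in the protocol. If the spread shrinks, the error runs the other way. The same applies to HAMD-17, PSS, PCL-C, ISI and SF-12.

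**Working it through.** **Inputs from the protocol.** Visits at Weeks 3, 6 and 12; 55 women per arm; 20% dropout, so 55 × 0.8 = 44 completers per arm; SD 10.8; difference 6.55; two-sided 5%; power 80%.

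**Assumed, because the protocol does not give them.** The SDs at each visit and the correlations between visits. In the growing-spread cases, 10.8 is taken as the Week 12 SD.

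**1. The plan's own figure.** The section states that "the results indicating an approximately difference of 6.55 in the BDI-II score between two groups". Per arm, n = 2 × (1.96 + 0.84)² × 10.8² / 6.55² = 2 × 7.85 × 116.64 / 42.90 ≈ 42.7, hence 43, and 43/0.8 = 53.75, hence 54. The t-based calculation gives 44, and 44/0.8 = 55. The stated 55 is reproduced. It is a two-sample calculation and does not depend on the model's covariance.

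**2. Week 12 difference, complete data.**

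- Standard error used by the model: √(mean of the three visit variances × 2/44)
- Actual standard error: SD at Week 12 × √(2/44)
- Ratio r = model SE / actual SE
- True two-sided error at nominal 5%: 2 × [1 − Φ(1.96 r)]

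For 9/10/10.8, for example, the mean variance is (81 + 100 + 116.64)/3 = 99.21. The model SE is √(99.21 × 2/44) = 2.124, against 10.8 × √(2/44) = 2.303, so r = 0.922.

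| Assumed SD, Weeks 3/6/12 | Mean variance | Model SE | Actual SE | r | True error |
|---|---|---|---|---|---|
| 10.8/10.8/10.8 | 116.64 | 2.303 | 2.303 | 1.000 | 5.0% |
| 9.8/10.3/10.8 | 106.26 | 2.198 | 2.303 | 0.954 | 6.1% |
| 9/10/10.8 | 99.21 | 2.124 | 2.303 | 0.922 | 7.1% |
| 8/9/10.8 | 87.21 | 1.991 | 2.303 | 0.865 | 9.0% |
| 7/8.5/10.8 | 79.30 | 1.899 | 2.303 | 0.825 | 10.6% |
| 12/11/10 | 121.67 | 2.352 | 2.132 | 1.103 | 3.1% |

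Simulation with 44 per arm gave 6.9%, 9.0% and 10.4% for 9/10/10.8, 8/9/10.8 and 7/8.5/10.8. An unstructured covariance gave 4.9% to 5.3% in the same cases.

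**3. Check with the model fitted by REML.** This used 110 women, a baseline covariate, SDs 8/9.5/10.8, a correlation of 0.8 per 3 weeks decaying with time, and 8,000 runs.

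- No dropout: mean model SE 1.815 against an empirical SD of 2.088; coverage of the nominal 95% interval 90.7%.
- 20% dropout: 1.944 against 2.232; coverage 91.4%.
- Equal SDs of 10.8: coverage 94.7% and 94.3%.

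Baseline adjustment and dropout therefore do not remove the effect.

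**4. Unequal spacing of visits.** With equal SDs and correlations of 0.75, 0.65 and 0.45, the Week 12 test stays at 5.0%. For this contrast, only unequal variance matters.

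**5. The other quantities the protocol could report.** With growing SDs, the random-intercept F test of the interaction had a true error of 5.1% to 5.3% under a constant correlation of 0.6, and 5.6% to 6.4% under the decaying correlations of step 4. With equal SDs and decaying correlations it was 5.7%, so the decay explains most of the small excess. The visit-averaged treatment difference had 4.8% to 5.3%.

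**The case against.** The strongest reply is that the affected quantity is not the one on which the protocol decides. The claim rests on the interaction, and step 5 shows that test close to nominal. The interval is not tied to Week 12. This stands, and it limits the point to visit-specific differences and their intervals.

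Second, nothing in the protocol shows that the spread grows. This also stands: one SD is given, the entry floor restricts baseline rather than the post-baseline visits, and 12/11/10 reverses the direction. The largest figure needs a Week 12 variance 2.4 times that at Week 3 (116.64/49).

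Third, residual covariance is ordinary SAP content, and a repeated-measures model does not exclude one. This stands in part. An SAP that is not shown may add a structure. But the protocol is not silent: it names one covariance term, and an SAP that followed it literally would inherit compound symmetry.

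A reader might infer that the primary test runs at about twice its nominal error. The documents do not support that: the 10% figure belongs to a Week 12 contrast under the steepest growth in the table. A reader might also take baseline as one of the modelled visits, in which case decaying correlation alone could distort the change to Week 12. The stated adjustment for baseline points to a covariate instead.

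**Conclusion.** The point holds in a limited form. As written, the model gives visit-specific differences a standard error that is right only if BDI-II variance is the same at Weeks 3, 6 and 12. Under assumed growth in spread, the true error of a nominal 5% Week 12 test is about 6% to 10.5%; under assumed shrinkage it is about 3%. Neither direction can be settled from the protocol. The conclusion assumes that the subject effect is a random intercept with independent residuals, that baseline is a covariate, and that visit-specific differences will be reported. The weakness is moderate, and it is worth correcting because a better covariance is available at almost no cost.

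**What to change.** In the primary model, replace the subject random effect with an unstructured within-subject covariance over Weeks 3, 6 and 12, using Kenward-Roger degrees of freedom. Name in advance a fallback for non-convergence that keeps visit-specific variances, such as heterogeneous compound symmetry. State the same for the other continuous outcomes, and fix the choice before unblinding.

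The cost is one or two sentences. An unstructured covariance over three visits has six parameters against two for the random intercept, so four more, which is negligible with 110 women. The sample size stays at 55 per arm. A baseline × visit term is optional and not needed to cure this weakness.

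### The primary efficacy criterion is a visit × treatment interaction, which is not the 6.55-point group difference the trial is sized for, has no direction, and has only 5% power for a constant benefit if baseline is a covariate only.

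*Protocol*

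**What the plan says.** Section C(iv), Data analysis, specifies a linear mixed-effects model with repeated measures for BDI-II, "with adjustment for the baseline; visit, treatment, and the visit" × treatment interaction as fixed effects, and subject as the random effect. The next sentence gives the criterion: "A significant two-way interaction will be considered to demonstrate whether the treatment group has a greater change in the BDI-II score". That sentence goes on to describe the change as running from baseline to the assessment visits. The size of the effect is then to be estimated by the treatment difference with a 95% confidence interval. No visit is attached to that difference, and it is not called the test. Other continuous outcomes are to be handled in a similar way. On the test level: "Statistical significance is defined as a two-tailed" P below 0.05.

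Section C(i)(c), Estimation of sample size, rests on a simple comparison of two groups: "the results indicating an approximately difference of 6.55 in the BDI-II score between two groups", with "a conservatively assumed standard deviation of 10.8", 80% power and "a dropout rate of 20"%, giving 55 per group. No time point is given for the 6.55.

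Section C(iii)(a), Clinical assessment, places assessments at baseline and Weeks 3, 6 and 12. It justifies Week 3 by earlier studies "showing that the significant improvement was observed at as early as at Week 3".

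**The concern.** Once baseline is a covariate, the outcome vector holds only the post-baseline visits. A treatment benefit common to those visits then sits in the treatment term, and the interaction holds only departures from that common benefit. A criterion based on the interaction therefore asks whether the benefit changes over time, whereas Aim 1 asks whether there is a benefit.

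Two consequences follow. A real and sustained benefit could miss the stated criterion, and a benefit that has disappeared by the end of treatment could meet it. In addition, the 80% power in the sample-size section belongs to a different test from the one that the analysis section makes decisive.

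**Working it through.** **Inputs from the protocol.** Difference 6.55; SD 10.8; two-sided alpha 0.05; power 80%; dropout 20%; 55 per group; visits at baseline and Weeks 3, 6 and 12.

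**Assumptions, not in the protocol.** 44 completers per arm (55 × 0.8). The SD of 10.8 applies to the score at each visit. The within-subject correlation r is 0.3, 0.5 or 0.7 and equal for all pairs of visits, which is the structure a random subject intercept implies.

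**Step 1: the plan's own figure.** Standardised difference = 6.55/10.8 = 0.606. Normal formula: n = 2 × (10.8 × (1.960 + 0.842)/6.55)² = 42.7, so 43 per arm. With the t distribution, n = 44 per arm, with power 80.3%. Then 44/0.8 = 55. The stated sample size reproduces, as a two-sample comparison of one mean difference.

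**Step 2: what the interaction tests.** Let d_j be the true group difference at visit j and d̄ their mean over the k visits in the response. The interaction F test has k − 1 and (k − 1)(2n − 2) degrees of freedom and noncentrality

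λ = Σ(d_j − d̄)² / [10.8² × (1 − r) × 2/n].

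If all d_j are equal, λ = 0 and power equals alpha, for any effect size, n or r.

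**Step 3: power with n = 44 per arm.** Reading A: baseline is a covariate only, k = 3, 2 and 172 df. Reading B: baseline is a fourth visit with a true difference of 0, k = 4, 3 and 258 df. Each cell gives r = 0.3 / 0.5 / 0.7.

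| Benefit at Weeks 3 / 6 / 12 | Σ(d_j − d̄)², A | Power, A | Σ(d_j − d̄)², B | Power, B |
|---|---|---|---|---|
| 6.55 / 6.55 / 6.55 | 0 | 5 / 5 / 5% | 32.18 | 69 / 84 / 97% |
| 4.4 / 5.5 / 6.55 | 2.31 | 10 / 12 / 17% | 24.86 | 56 / 72 / 92% |
| 1.64 / 3.28 / 6.55 (linear in time) | 12.51 | 35 / 47 / 70% | 23.46 | 53 / 70 / 91% |
| 6.55 / 3 / 0 (gone by Week 12) | 21.50 | 56 / 72 / 91% | 29.10 | 64 / 80 / 96% |

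Worked example, last row, reading A, r = 0.5: the denominator is 116.64 × 0.5 × 2/44 = 2.651, so λ = 21.50/2.651 = 8.11. Against the critical F of 3.05 this gives 72%.

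Simulation (4,000 trials per setting) of the constant benefit gave 4.7% to 5.9% under reading A, and 68%, 83% and 98% under reading B, in line with the formula.

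**Step 4: the contrast that matches the sample size.** For a difference of 6.55 at one visit, adjusted for a baseline with correlation r, the residual SD is 10.8 × √(1 − r²) = 10.30 / 9.35 / 7.71. The noncentrality 6.55/(SD × √(2/44)) is 2.98 / 3.28 / 3.98, and power is 84% / 90% / 98%. With no gain from baseline it is the planned 80%.

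**The case against.** The strongest reply is that the authors meant reading B. Their sentence speaks of change from baseline to the assessment visits. A visit × treatment interaction measures that only if baseline is one of the visits, and the protocol never lists which visits form the response. Under reading B a sustained benefit is detected with reasonable power. This stands, and it limits the point. A reader might infer that an effective treatment is bound to fail the primary test; the document does not support that, because the 5% figure holds only if baseline is a covariate and not also a response. But reading B conflicts with the stated baseline adjustment: baseline as both covariate and response is regressed on itself.

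A reader might also infer that the protocol predicts an effect that is present at Week 3 and then flat. It does not. The Clinical assessment section cites early improvement to justify the first visit. It does not say that this was a between-group difference, or that it then stayed level. A benefit that begins by Week 3 and grows is equally consistent with the text.

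Nor does the protocol say that 6.55 is a Week 12 difference; no time point is stated.

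Finally, the treatment difference with its confidence interval is to be reported, so a sustained benefit would be visible. That softens the consequence, but the protocol makes the interaction, not that interval, the evidence of efficacy. Leaving the visit of the estimate to a statistical analysis plan would be normal and is not a fault in itself.

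**Conclusion.** The criterion is wrong as written. The text supports two incompatible models, and for the same constant 6.55-point benefit they give 5% power in one and about 69% to 97% in the other.

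Two faults hold on either reading. First, the test has no direction: a benefit that is gone by Week 12 would be significant in about 56% to 96% of trials. Second, it is not the test the trial was sized for. The 80% power belongs to a single two-group difference. In the two growing-benefit profiles examined, the interaction has 10% to 70% power on reading A and 53% to 92% on reading B, so 80% is not assured.

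The 5% result depends on reading A but on no assumed correlation. All the other interaction figures rest on r between 0.3 and 0.7, equal correlation between visits, an SD of 10.8 at every visit and 44 completers per arm.

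**What to change.** In Data analysis, replace the interaction criterion with wording such as: the primary test is the treatment difference in BDI-II at Week 12, estimated as a contrast from the baseline-adjusted repeated-measures model with Weeks 3, 6 and 12 as responses, at two-sided alpha 0.05; Weeks 3 and 6 are supportive and the visit × treatment interaction is descriptive. Week 12 is the natural choice because it is the end of the 12-week treatment period, but the essential step is to name one visit and make its contrast the test.

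In Estimation of sample size, state which time point the 6.55 refers to, after checking its source, so that it matches the chosen contrast. Use the same contrast for the other continuous outcomes.

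The cost is wording in the protocol and the analysis plan. No new data, visits or participants are needed. On the protocol's own 6.55 and SD, the planned 55 per group still gives at least 80% power after dropout, if 6.55 applies at the named visit.
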